**Demographic information**
Exact age (measured in years to 2 decimal places)Sex (male or female)RaceHeight (measured in inches)Weight (measured in pounds)Head circumference (measured in inches)Cleft type
**Hearing information**
Hearing status (tympanometry; pass or fail and date)Ear infections (yes or no and how many if yes)Other hearing information
**Speech information**
Speech therapy (yes or no; if yes, when and what was targeted)Ages and Stages Questionnaire, Third Edition (complete form)MacArthur-Bates Communicative Development Inventories (complete form)
**Surgical information**
Palate repair (intravelar veloplasty or double-opposing Z-plasty; date; whether there was adjunct tissue; and, if yes, whether it was buccal fat flaps or buccal myomucosal flaps)Pressure-equalizing tubes (yes or no and the date if yes)

Two independent raters will measure the speech and/or MRI data. The primary rater will be blind to the participant demographics to reduce bias. This will be achieved through controlling access to participant demographics and deidentifying the raw data for analysis.

### Evaluation Outcomes

The primary outcomes correspond to the 2 study aims. For aim 1, the primary outcome is the type of surgical procedure performed (IVV or DOZ with or without adjunct tissue use) predicted by preoperative anatomical variables, namely, cleft width and LVP muscle length. For aim 2, the primary outcome is the diversity of oral stop consonants produced at 18 months, serving as a functional measure of velopharyngeal competence. Secondary outcomes include additional anatomical measures (effective velar length, effective velopharyngeal ratio, and LVP muscle continuity) and developmental and language scores. Anatomical variable definitions are outlined in Table 1. Exploratory tertiary outcomes will examine modifiers of anatomy and speech, including sex, demographic characteristics, tympanometry results, and other developmental assessments. Missing data will be imputed (when appropriate) or addressed using pairwise deletion. Additionally, data may be analyzed cross-sectionally to meet the study aims.

**Table 1 table1:** Anatomical variables and corresponding definitions as obtained from magnetic resonance imaging for aims 1 and 2.

Variable	Definition
Cleft width	Distance between the lateral margins of the cleft at the widest point
Effective VP^a^ ratio	Effective velar length/pharyngeal depth
Effective velar length	Length of the velum from the posterior hard palate to the LVP^b^ muscle
LVP muscle angle of origin	Interior angle created by the lines drawn to measure distance between the origin points and LVP muscle length
LVP muscle continuity	Whether the LVP muscle is continuous through the midline (yes or no)
LVP muscle length	Length of the LVP muscle along one side from origin to insertion
Origin-origin distance	Distance between the points of origin of the LVP muscle
Pharyngeal depth	Distance from the posterior hard palate to the posterior pharyngeal wall at the palatal plane
VP ratio	Total velar length/pharyngeal depth
Velar insertion distance	Distance between the locations where the bilateral LVP muscle bundles insert into the body of the velum (ie, repaired velar width)
Velar length	Length of the velum from the posterior hard palate to the tip of the uvula
Velar thickness	Distance from the velar knee to the velar dimple

^a^VP: velopharyngeal.

^b^LVP: levator veli palatini.

Due to the observational nature of this study, there are minimal and foreseeable risks, primarily related to potential anxiety or fear associated with the MRI procedure. No sedation will be used, and all established MRI safety screening and monitoring procedures of the clinical site will be followed [44]. All events will be documented and managed according to institutional safety protocols. Caregiver questionnaires and clinical data will be entered into a secure REDCap (Research Electronic Data Capture; Vanderbilt University) database [45] with routine quality checks to maintain accuracy and completeness. Study data will be deidentified and securely stored on institutional servers. Access to study data will be limited to authorized research staff. After study completion, participants will continue standard clinical follow-up through the craniofacial team; no additional interventions beyond standard care are required.

### Statistical Analysis

All participants with data at the relevant time points will be included in each analysis. The primary outcome will be evaluated using binomial logistic regression to determine how preoperative anatomical variables predict surgical procedure selection, controlling for sex, race, and cleft type. Principal component analysis may be applied to reduce dimensionality among anatomical predictors. The secondary outcome will be assessed using a 2-way analysis of covariance examining the effects of surgical type and number of oral stops on postsurgical anatomical measures, controlling for sex, cleft type, and developmental and language scores.

To ensure scientific rigor, intrarater and interrater reliability will be calculated for both MRI and speech measures. Independent raters will measure MRI scans and consonant productions following completion of a structured reliability training protocol to enhance measurement accuracy and precision. This training will consist of a guided review of the velopharyngeal MRI and speech literature, a detailed study of relevant cleft MRI anatomy and speech characteristics, and repeated practice measurements of both typical children and those with cleft palate until a predetermined level of agreement is reached. Each measurement training cycle will be followed by discussion-based debriefing and troubleshooting. The primary rater will measure all samples, whereas a second rater will measure a randomly selected 10% of the samples to calculate interrater reliability. The primary rater will rerate a random selection of 10% of the samples to calculate intrarater reliability.

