### Aims of This Study

In summary, recent studies quantifying the velopharynx in children have generally examined anatomy and physiology in isolation [35], and many have relied on cross-sectional designs [15,32]. Few have tracked both anatomical and functional measures at 2 time points within the same individual. Multidimensional data before and after palatoplasty are crucial for understanding how palate repair influences both velopharyngeal structure and function. These individualized assessments are key for translating basic science findings into patient-specific surgical planning and targeted interventions. This protocol aims to take an essential step toward precision medicine in infants with cleft palate.

This study combines nonsedated MRI–based anatomical assessment with functional speech measurements in the same infants before and after palatoplasty. By linking patient-specific anatomy before and after palate repair to early speech outcomes, we aim to establish data-driven criteria for individualized surgical planning and targeted speech monitoring. This approach addresses a critical gap by providing quantitative, objective measures of surgical success and velopharyngeal development, moving beyond subjective assessment. Ultimately, these findings may lead to work that reduces persistent speech deficits, prevents multiple surgeries, and lessens the associated psychosocial and financial burden of cleft palate. Specifically, this study has two primary aims:

To establish which presurgical anatomical variables are predictive of surgical procedure selection based on perceptual assessment of intraoperative tension for palate repair (hypothesis: preoperative cleft width and LVP muscle length are predictive of surgical procedure selection based on intraoperative tension of palatal tissue)To determine which postsurgical anatomical features are associated with the greatest diversity in oral stop consonant production at 18 months in children with repaired cleft palate (hypothesis: a longer velum, greater effective velopharyngeal ratio, and continuity of the LVP muscle are associated with greater diversity of oral stop consonants by 18 months but not with procedure type)

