### Participants and Recruitment

A total of 30 participants will be recruited from the Children’s Hospital Colorado Cleft Lip and Palate Program (Aurora, Colorado), with an initial enrollment of 39 to account for an anticipated 30% attrition due to MRI motion artifacts, refusal, or missed visits. This sample size was selected based on the pilot nature of this work and use of a single recruitment site; furthermore, the sample size is consistent with prior prospective studies using nonsedated MRI of the velopharynx in children [33,36,37]. This study is considered exploratory to evaluate the relationship among anatomy, surgical selection, and early speech outcomes, as well as to support future larger-scale, multicenter studies. The recruitment site receives 50 to ⁠60 new referrals each year, providing ample opportunities to reach the target sample size over the 3-year funding period. Retention strategies will be used to reduce dropout, including regular personalized reminders, flexible scheduling, and incentives. Participants must be from English-speaking families and have a diagnosis of cleft palate that has not yet been repaired. Infants diagnosed with syndromes prior to 18 months (as reported in their medical chart), those ineligible for MRI (eg, metal implants or severe airway anomalies), or those with other contraindications to standard surgical care will be excluded. Those scheduled for primary palatoplasty after 15 months of age will also be excluded from this analysis.

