## Discussion

### Expected Findings

This pilot study will explore the relationship between patient-specific anatomy before and after palate repair and early speech outcomes. Modern attempts to report quantitative measures of the velopharynx in infants have investigated its anatomy [30,46,47] and physiology [20,34,35,48] independently of one another and have commonly used a cross-sectional study design rather than comparing these variables within the same individual over time. Multidimensional data that encompass measures of both anatomy and physiology within the same individual over time are essential for examining how primary palatoplasty affects velopharyngeal form and function at the level of the individual patient. Individualized presurgical planning and responses to surgical treatment are essential for translating basic science findings into valuable patient-specific intervention protocols. This proposal has been designed to take this important step to facilitate precision medicine in this population. Preliminary, data-driven criteria for individualized surgical planning and targeted speech monitoring will be established as a result of this work. Pending a larger, multisite investigation, this work may have future implications to improve and individualize surgical interventions for primary palatoplasty.

Aim 1 will determine which anatomical variables from those used in previous investigations [30,46] can predict the type of surgery received, quantifying the surgical decision-making process objectively using MRI and reducing reliance on surgeon experience to make this decision. We hypothesize that certain anatomical parameters, namely, palatal width and LVP muscle length (Figure 2), may be predictive of surgical procedure selection. If this is the case, this study will provide a quantified, anatomical basis for individualized surgical interventions to support successful palatoplasty and potentially reduce VPI. Alternatively, if there is no anatomical link between patient-specific, presurgical anatomy and surgical decision-making, a more complex, multidimensional analysis of surgical decision-making factors is warranted to improve outcomes of primary palatoplasty and subsequent rates of VPI.

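### Aim 1 treats an adjusted logistic association in about 27–30 infants as prediction and as a basis for surgical-planning criteria, with no optimism-corrected performance tied to the claim

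*Protocol article*

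**What the plan says.** The Statistical Analysis section gives one analysis for Aim 1: "binomial logistic regression to determine how preoperative anatomical variables predict surgical procedure selection, controlling for sex, race, and cleft type". PCA of the anatomical predictors is optional. Surgical Considerations adds adjustment for surgeon (five operate) if surgeons differ.

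Evaluation Outcomes describes the procedure as "predicted by preoperative anatomical variables, namely, cleft width and LVP muscle length". Expected Findings is wider: "Aim 1 will determine which anatomical variables from those used in previous investigations [30,46] can predict the type of surgery received".

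On numbers, Participants and Recruitment says: "A total of 30 participants will be recruited from the Children’s Hospital Colorado Cleft Lip and Palate Program", "with an initial enrollment of 39 to account for an anticipated 30% attrition due to MRI motion artifacts, refusal, or missed visits". The justification is practical: "This sample size was selected based on the pilot nature of this work and use of a single recruitment site".

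On use of the result, Aims of This Study says "we aim to establish data-driven criteria for individualized surgical planning and targeted speech monitoring". Expected Findings says the anatomical variables "can predict the type of surgery received, quantifying the surgical decision-making process objectively using MRI and reducing reliance on surgeon experience". The same section calls the resulting criteria preliminary and makes wider implications conditional on a larger multisite study.

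**The concern.** Saying that a variable predicts the procedure, or that it can reduce reliance on the surgeon's experience, is a claim about infants not yet seen. The stated analysis fits one model once, to everyone with data. Its coefficients and fit describe these infants. With few infants per parameter, the fit also flatters the model because it is measured on the data that estimated it.

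Expected Findings allows for two outcomes: anatomy predicts and gives a basis for individualized surgery, or there is no anatomical link. It leaves no room for an apparent link that does not carry over to new infants. The limitations mention reduced ability to detect subtle effects and limited applicability, but not optimism. At stake is whether criteria carried into the larger study, and into the later trial matching patients to techniques, rest on real predictive performance.

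**Working it through.** **Sample size.** The stated enrolment reproduces as 30 × 1.30 = 39. After 30% attrition, 39 × 0.70 = 27.3 infants remain, hence about 27–30. (Retaining 30 would need 30 / 0.70 = 42.9, so 43; that is a side point.) Aim 1 needs only the presurgical scan, so its N could approach 39. The target of 30 has no power inputs to recompute.

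**Parameters.** Two anatomical terms (cleft width, LVP muscle length) plus sex (1), race and cleft type. The article does not give category counts, so I assume:
- 2 levels each: 2 + 1 + 1 + 1 = 5 parameters;
- 3 levels each: 2 + 1 + 2 + 2 = 7 parameters.

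The IVV/DOZ split is also not given; I assume 50:50 to 30:70. Infants in the smaller group per parameter: at best 15 / 5 = 3.0 (N = 30, 50:50); with N = 27 and 30:70, about 8 / 7 = 1.1.

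**Apparent discrimination under no signal.** Simulate predictors unrelated to procedure, fit the logistic model, and compute AUC in the fitting data and in new infants. Optimism = apparent AUC − new-infant AUC.

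| Model, N = 27–30 | Median apparent AUC | New infants | Optimism |
|---|---|---|---|
| Two named predictors only | 0.62–0.66 | 0.50 | 0.12–0.16 |
| Plus sex, race, cleft type (5–7 parameters) | 0.71–0.82 | 0.50 | 0.21–0.32 |

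Sensitivity, with splits extended to 20:80:
- 8 parameters (3-level race, 4-level cleft type), N = 27–30: 0.80–0.90.
- 12 parameters (the 8 plus 4 surgeon terms), N = 27–30: 0.88–1.00.
- N = 39: 0.69–0.74 with 5 parameters and 0.75–0.81 with 8.
- Noise reaches an apparent AUC of at least 0.70 in 63–88% of datasets with 5 parameters, and in 19–45% with the two named predictors alone (N = 27–30).

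**The other reading of predictive.** Test the two anatomical terms given the covariates: LR = 2 × (log-likelihood with anatomy − log-likelihood without), compared with chi-square on 2 df at 0.05. At N = 27–30 noise passes in about 6–22% of datasets against a nominal 5%. The 22% arises with N = 27, 8 parameters and a 20:80 split. Requiring at least one significant Wald test instead, noise passes in about 1–10%.

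**A tempting remedy, checked.** Suppose a variable is called predictive whenever leave-one-out AUC rises. Adding two noise variables raises it in 40–55% of null datasets. AUC and Brier score both improve in about 9–18%. The bare rule is therefore looser than the nested test.

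**The case against.** The strongest reply is that the article never says the model will be judged by its apparent fit. It names no AUC, accuracy, cut-off or success threshold, and its wording about controlling for covariates reads most naturally as inference on the anatomical terms. Internal validation may sit in an analysis plan that is not shown, so its absence here is not itself a fault. A reader might infer that pure noise would routinely be reported as good prediction. The text does not support that: it requires a whole-model criterion the plan does not state, and on a term-by-term reading noise passes in a minority of datasets.

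Three further points also stand. Much of the inflation in the adjusted model comes from the covariates rather than from anatomy. The objection that the model mixes anatomy with cleft type, sex and race fails, because adjusted coefficients or a nested test do isolate what anatomy adds. And the article calls itself a pilot, labels the criteria preliminary, defers to a multisite study, and withholds study MRI findings from surgeons, so no infant in this study is managed on the result.

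The replies do not reach the mismatch between analysis and claim. A significant adjusted coefficient is still an association, while the predictive conclusions and the planning criteria are stated in the article itself.

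**Conclusion.** The concern holds in a limited form. The one stated analysis supports association between anatomy and procedure in this cohort; it does not support a claim about new infants or a basis for planning criteria. Any discrimination figure taken from the adjusted fit would need a correction of about 0.21–0.32 AUC under the null (0.12–0.16 for the two named predictors alone). These sizes rest on assumed category counts and procedure splits and on N of 27–30; they shrink at N = 39 and grow with surgeon terms or a wider anatomical pool. If the nested test is the criterion, the problem is a false-positive rate of roughly 6–22%, not near-certain false prediction. This is worth correcting, but it does not invalidate Aim 1 as an exploratory question.

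**What to change.** - Make the Aim 1 inference a nested test of cleft width and LVP muscle length given the covariates, in a form suited to small samples (for example a penalised-likelihood or permutation test). Describe a positive result as an association.
- Report any discrimination, accuracy or cut-off only after bootstrap optimism correction or cross-validation, with an interval, and for the model with and without the anatomical variables. Repeat any PCA, surgeon-adjustment or cut-off step inside each resample.
- Do not use a rise in out-of-sample AUC by itself as the decision rule.
- In the aims and in the reporting of results, reserve the terms predictive and criteria for performance validated in the planned larger study.

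The cost is a little analysis code, some rewording and a less favourable performance figure. No new data are needed, and Results states that analysis has not begun.

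### Aim 1 is about two named variables, but the optional PCA does not exempt them; a model on component scores could neither confirm nor refute that hypothesis

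*Protocol article*

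**What the plan says.** The protocol article sets Aim 1 at the level of individual variables in three places.

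- **Aims of This Study:** the aim is "To establish which presurgical anatomical variables are predictive of surgical procedure selection based on perceptual assessment of intraoperative tension for palate repair". The hypothesis is that "preoperative cleft width and LVP muscle length are predictive of surgical procedure selection based on intraoperative tension of palatal tissue".
- **Evaluation Outcomes:** the primary outcome is the procedure performed, "predicted by preoperative anatomical variables, namely, cleft width and LVP muscle length".
- **Expected Findings:** "Aim 1 will determine which anatomical variables from those used in previous investigations" can predict the surgery received. Palatal width and LVP muscle length are again singled out.

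The Statistical Analysis section describes the model only in general terms: "binomial logistic regression to determine how preoperative anatomical variables predict surgical procedure selection, controlling for sex, race, and cleft type". The next sentence reads: "Principal component analysis may be applied to reduce dimensionality among anatomical predictors". It does not say whether cleft width and LVP muscle length stay in the model as themselves if this option is used.

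On size, the target is 30 infants, "with an initial enrollment of 39 to account for an anticipated 30% attrition due to MRI motion artifacts, refusal, or missed visits", and "This sample size was selected based on the pilot nature of this work and use of a single recruitment site".

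**The concern.** Cleft width and LVP muscle length are anatomical predictors, so the PCA sentence covers them as written. Reducing the dimension of a predictor set before a regression normally means entering component scores in place of the measures. A component is built from the variance that the measures share, without reference to the procedure chosen, and it mixes all its inputs. Its coefficient therefore does not answer which variable predicts.

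Two errors become possible. A component can be significant because of other anatomy when neither named variable plays a part. A component can also be null when the named variables do matter, because their contribution is diluted or cancels. Either would leave the primary Aim 1 question unanswered. Expected Findings says that a positive result would give a quantified anatomical basis for individualised surgery, so the distinction matters for how the result is used.

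**Working it through.** **Nothing to reproduce.** The article gives no alpha, power, effect size or correlation for Aim 1. The check is a comparison of the sections above plus an illustrative simulation.

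**Inputs from the article:** n = 30 (Participants and Recruitment); logistic regression (Statistical Analysis); two named predictors (Aims of This Study, Evaluation Outcomes). Table 1 lists 12 measures for both aims and does not mark the presurgical ones.

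**Assumptions:** 10 standardised measures with a common pairwise correlation ρ of 0.2 or 0.5; effects in log-odds per SD (1 is an odds ratio of e^1 = 2.7, 0.3 is e^0.3 = 1.35); 5% level; no covariates; about 2000 runs. Likelihood-ratio tests compare the first component (PC1, 1 df) with cleft width plus LVP length (2 df).

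| Truth | ρ | PC1 rejects | Direct test rejects |
|---|---|---|---|
| Only the two matter, +1 and -1 | 0.2 | 7.4% | 76.4% |
| | 0.5 | 6.6% | 58.1% |
| Only the two matter, +1 and +1 | 0.2 | 57.0% | 86.6% |
| | 0.5 | 86.3% | 91.7% |
| Neither matters, other eight at 0.3 | 0.2 | 79.4% | 21.2% |
| | 0.5 | 96.2% | 66.4% |
| Nothing matters | 0.2 | 4.9% | 6.9% |
| | 0.5 | 5.2% | 6.5% |

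**Why the pattern arises.** With equal correlations, PC1 weights each measure 1/√10, so the two named variables carry 2/10 = 20% of the squared loadings (simulated: 20%). The variance of PC1 is λ = 1 + 9ρ, which is 2.8 at ρ = 0.2 and 5.5 at ρ = 0.5. The covariance of PC1 with the linear predictor is λ × (sum of effects)/√10.

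- Opposite signs: the sum is 1 - 1 = 0, so PC1 carries no signal.
- Same sign: the correlation of PC1 with the linear predictor is (2/√10) × √(λ/(2 + 2ρ)). At ρ = 0.2 this is 0.632 × √(2.8/2.4) = 0.68. At ρ = 0.5 it is 0.632 × √(5.5/3) = 0.86. The power loss falls from 86.6 - 57.0 = 29.6 points to 91.7 - 86.3 = 5.4 points.

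**Reading the third setting.** The direct test also rejects there (21.2% and 66.4%), because the named variables are correlated with the true drivers and the test does not adjust for them. The clean comparison has zero correlation. With 11 measures, n = 27 to 30 (39 × 0.70 = 27.3) and an uncorrelated velar length driving the choice, component tests rejected in 22% to 58% of runs, depending on how the measures were generated and how many components were kept. The direct test rejected in 4% to 6%.

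**Other settings with 11 measures.**

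- Opposite signs: components 4% to 38%, direct 47% to 85%.
- Same sign, PC1 only: the loss was about 14 to 18 points at a correlation of 0.4 and 3 to 5 points at 0.6.
- Four measures (cleft width, LVP length, LVP angle, origin-origin distance), same sign: direct 88% against PC1 83% at 0.4, and 92% against 93% at 0.6.

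**The case against.** The strongest reply is that substitution is inferred. The text says only that PCA may be used. Evaluation Outcomes names the two predictors, and two predictors need no reduction, so a natural reading is that PCA would serve the wider Table 1 set. With about 30 infants, many correlated measures and three covariates, dimension reduction is defensible for the wider question of which measures predict. The study calls itself a pilot and exploratory. The variable list, the trigger for PCA and the retention rule may properly sit in an analysis plan that is not shown.

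Much of this stands. The absence of those details is not criticised here. What remains is internal to the article: a variable-level primary hypothesis beside an option that, as worded, reaches the same two variables.

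A reader might also infer three stronger things that the documents do not support:

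- That the plan will replace the two variables. PCA is optional and its scope is left open.
- That a significant component would be reported as evidence for cleft width or LVP length. No section says so. Loadings can be inspected, although that is not an unconstrained test of each variable.
- That PCA always costs a large amount of power. It does not when the measures are strongly correlated and the effects share a sign.

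Nor does the article state a formal null hypothesis or significance level for Aim 1.

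**Conclusion.** The point holds in conditional form: if component scores replace cleft width and LVP muscle length, the primary Aim 1 model cannot confirm or refute the hypothesis that names them. This follows from the wording and does not depend on the simulation.

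The simulation shows the direction and the range. A component test can be significant when neither named variable matters. It can lose much of the power to detect them when the measures are weakly correlated or the effects have opposite signs. The loss is small when correlation is strong and the signs agree.

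All rates rest on assumed correlations, effects and measure sets, and they omit sex, race and cleft type. Adding five covariate degrees of freedom lowered direct power by about 6 to 15 points in a check, so the direct figures are optimistic in absolute terms. For an exploratory pilot this is of moderate weight, and worth settling now: as of April 4, 2026, 8 participants were enrolled and analysis had not begun.

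**What to change.** Replace the PCA sentence in Statistical Analysis with wording such as: *Cleft width and LVP muscle length enter the primary Aim 1 logistic model as separate predictors and are not entered into a principal component analysis. Any principal component analysis is limited to the remaining Table 1 measures and is reported as exploratory.*

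Two refinements are optional: a joint 2-df test of the two variables alongside their individual estimates, and leaving the two velopharyngeal ratios out of any PCA that already contains their numerators and pharyngeal depth.

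The cost is a sentence or two of analysis text, with no new data or participants. The small downside is that dimension reduction is no longer available for the two primary predictors.
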